In the RCT phase, we will test the intervention’s efficacy comparing the meta self-efficacy intervention to a placebo. The goal is to assess the basic effect that the meta self-efficacy intervention can produce while controlling for the expectation bias [24]. We will additionally compare treatment credibility between conditions. Although meta self-efficacy is potentially applicable universally across life domains, testing its enhancement within the framework of the theory by Bandura requires concentrating on a specific background. In particular, enhancing meta self-efficacy should, in principle, lead to improvements in domain-specific self-efficacy. In this study, we test the effects of improving meta self-efficacy in the occupational context and among young employees, expecting that enhancing meta self-efficacy will improve their work self-efficacy (primary outcome). Furthermore, strengthening meta self-efficacy should lead to further well-being benefits [10], which we will measure as multiple dimensions of occupational well-being. These will reflect job-related emotions, stress levels, and work capabilities, encompassing behaviors and values. Accordingly, the secondary outcomes include job stress [25], job affective well-being [26], and work capabilities [27]. We expect improvements in both primary and secondary outcomes immediately after the intervention, with effects sustained at follow-ups. Additionally, a secondary objective of the RCT phase is to examine how factors such as intervention engagement and adherence relate to the intervention’s efficacy.

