### RCT Phase

#### Study Design

To evaluate the efficacy of the meta self-efficacy intervention, we will conduct a 2-arm RCT. Participants will be randomly assigned (1:1) to 1 of 2 conditions: an experimental group with access to the meta self-efficacy–enhancing internet intervention or a placebo control group with access to educational content. A placebo comparator in the form of interactive educational content on occupational well-being has been chosen over a waitlist control [31] to avoid a typical expectation bias: participants in the intervention group usually expect improvement, whereas those on the waitlist do not. An active but nontherapeutic comparator delivered through the same modality as the intervention [24] will allow us to isolate the specific effect of the meta self-efficacy intervention while holding expectations similar in both groups. Outcomes will be measured at 4 time points: baseline, posttest, and 3- and 6-month follow-ups.

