#### Power Analysis

To determine the required sample size, we considered the effect sizes reported for internet interventions aimed at enhancing context-specific self-efficacy. These interventions have shown effect sizes of approximately *d*=0.5 for various stress-related outcomes [20,32]. However, the effect size for the meta self-efficacy intervention may differ and is likely smaller as it shifts the focus from enhancing self-efficacy in a specific context to bolstering the ability to leverage self-efficacy sources. To account for this, the trial is powered to detect a minimum meaningful effect of *d*=0.25. We conducted an a priori power analysis for a linear mixed-effects model using the *powerlmm* R package (R Foundation for Statistical Computing) [33]. Given 4 measurement points, an error level of α=.05, and power of 1 – β of 0.90, the analysis indicates that 600 participants are needed. This calculation factors in a 30% dropout rate based on a previous self-efficacy internet intervention for young adults and a broader review of adherence in mobile interventions [21,34].

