#### Meta Self-Efficacy Intervention

Following the definition of meta self-efficacy, the intervention will guide participants through understanding the mechanism of self-efficacy, introduce and practice meta self-efficacy strategies (leveraging the 4 sources), and foster the development habits that support the use of these strategies in everyday life. The intervention spans 3 weeks and consists of three components: (1) preparation stage and monitoring of daily challenges and self-efficacy beliefs, (2) learning to leverage self-efficacy sources, and (3) incorporating meta self-efficacy strategies in daily life. The intervention is grounded in the work on self-efficacy sources by Bandura [16]. All activities will be evaluated during the co-creation phase to reflect authentic strategies that individuals use to draw on self-efficacy sources. Crucially, the intervention will be tailored to young employees, ensuring that the activities are relevant to both workplace challenges and the experiences of individuals in early adulthood.

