##### Intervention Efficacy

The intervention’s efficacy will be evaluated for each outcome measure following the intention-to-treat principle, meaning that all randomized participants will be included in the final analysis. The primary efficacy analysis will use a linear mixed-effects model, with a random intercept for participants and fixed effects of time and condition [42]. Although the expected dropout rate is included in our a priori power analysis, we will also examine the actual dropout rate and its characteristics. This examination will determine whether there is a significant difference in dropout percentages between the 2 conditions, a phenomenon known as differential dropout [43]. Subsequently, we will apply an appropriate missing data imputation method and calculate pooled results using linear mixed-effects models (eg, using the *mice* and *mitml* R packages [44]). Sensitivity analyses will be conducted to examine the robustness of the results and compare intervention effect estimates across per-protocol, intention-to-treat, and imputed data analyses. Additionally, we will verify the credibility of the placebo in comparison to the intervention condition.

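### The random-intercept model assumes equal correlation over gaps of weeks and of months; if correlation falls with time, change-from-baseline standard errors would be too small at 6 months and too large at posttest

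*Protocol article*

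**What the plan says.** The Intervention Efficacy section states that "The primary efficacy analysis will use a linear mixed-effects model", "with a random intercept for participants and fixed effects of time and condition", and applies it to each outcome. The random intercept is the only within-person term stated. No random slope, residual correlation structure or robust standard error appears there or elsewhere in the article.

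The Study Design section states: "Outcomes will be measured at 4 time points: baseline, posttest, and 3- and 6-month follow-ups". The section on the intervention adds: "The intervention spans 3 weeks and consists of three components". The Procedure section places the two follow-ups after posttest. The gap from baseline is therefore about 3 weeks for the first post-randomisation assessment and more than 6 months for the last.

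The Study Aims section sets out what the model has to show: "We expect improvements in both primary and secondary outcomes immediately after the intervention, with effects sustained at follow-ups".

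The planned sensitivity analyses compare per-protocol, intention-to-treat and imputed results. None changes the covariance structure, and the imputed data sets are again analysed with linear mixed models.

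**The concern.** A random intercept with independent residuals implies compound symmetry: equal variance at each occasion and one common correlation for all six pairs. Repeated self-report scores on work self-efficacy, stress and affect usually agree more closely over 3 weeks than over half a year. A single pooled correlation would then be too low for the baseline-posttest pair and too high for the baseline-6-month pair.

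Two claims are at stake. The test of an immediate effect would be conservative and lose power. The test of a sustained 6-month effect would reject a true null hypothesis more often than the nominal 5%. The same structure serves the primary and all secondary outcomes.

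**Working it through.** **Inputs from the protocol article.** Four occasions; 3-week programme; 1:1 allocation; N = 600; alpha 0.05 (sidedness not stated, two-sided assumed); 30% dropout. The article gives no within-person correlation or ICC.

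**The plan's own figure.** The Power Analysis section says: "an error level of α=.05, and power of 1 – β of 0.90, the analysis indicates that 600 participants are needed". This cannot be reproduced from the stated inputs alone, because the ICC, slope variance and dropout pattern are missing. A random-intercept model with linear time, d = 0.25 at the last occasion and gradual 30% dropout needs 626 participants at ICC 0.60 and 550 at ICC 0.65. So 600 fits an ICC slightly above 0.6, and this point does not dispute it.

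**Assumptions.** Occasions at 0, 3, 16 and 29 weeks; outcome variance 1 throughout; exponential decay of correlation between the values given for 3 and 29 weeks.

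**Formula, complete data, 300 per arm.** For the between-arm difference in change from baseline to occasion t:
- true variance = 4(1 − rho(1,t))/300
- model variance = 4(1 − mean rho)/300, where mean rho averages all six pairs
- SE ratio (model/true) = sqrt[(1 − mean rho)/(1 − rho(1,t))]
- actual two-sided type I error = 2Φ(−1.96 × ratio)

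**Central case, 0.75 at 3 weeks falling to 0.50 at 29 weeks.** The correlations by lag are 0.75 (3 weeks), 0.642 (13 weeks, two pairs), 0.612 (16), 0.524 (26) and 0.50 (29). Their mean is (0.75 + 2×0.642 + 0.612 + 0.524 + 0.50)/6 = 0.612.
- Model SE at every occasion: sqrt(4×0.388/300) = 0.072.
- 6 months: true SE sqrt(4×0.50/300) = 0.082; ratio sqrt(0.388/0.50) = 0.88; type I error 8.4%.
- Posttest: true SE sqrt(4×0.25/300) = 0.058; ratio sqrt(0.388/0.25) = 1.25; type I error 1.5%.
- 3 months: rho is 0.612, equal to the mean, so the ratio is 1.00.

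**With dropout.** The best-fitting compound-symmetry covariance was found under the assumed true covariance, and its model-based SE was compared with the sandwich SE. Gradual dropout means 0, 10, 20 and 30% missing at the four occasions.

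| Correlation, 3 to 29 weeks | Dropout | 6-month SE ratio | 6-month type I error | Posttest SE ratio | Posttest type I error |
|---|---|---|---|---|---|
| 0.70 flat | none | 1.00 | 5% | 1.00 | 5% |
| 0.70 to 0.60 | 30% by posttest | 0.94 | 6.4% | 1.08 | 3.4% |
| 0.70 to 0.60 | gradual 30% | 0.94 | 6.7% | 1.08 | 3.5% |
| 0.75 to 0.50 | gradual 30% | 0.87 | 8.8% | 1.22 | 1.6% |
| 0.80 to 0.40 | none | 0.85 | 9.7% | 1.47 | 0.4% |
| 0.80 to 0.40 | gradual 30% | 0.83 | 10.3% | 1.42 | 0.5% |

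In the central case with gradual dropout, the 6-month SE is 0.081 reported against 0.093 true, and the posttest SE 0.074 against 0.061. An unstructured covariance gives 0.092 and 0.061, with type I error of 5% at both.

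**Other contrasts, same range of decays.** If both arms share a baseline mean, the 6-month ratio is 0.95 to 0.86 and the posttest ratio 1.06 to 1.28. For a raw between-arm difference at one occasion with complete data, the variance is 2/300 whatever the correlation, so the ratio is 1.00; with 30% dropout it is 0.96 to 1.05.

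**The case against.** Four objections deserve an answer.

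1. **The size rests on figures that the article does not give.** This stands. A reader might infer that the 6-month test is anti-conservative as planned. The article supports only a conditional statement, because with flat correlation nothing is distorted.

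2. **The stated model has no time-by-condition term.** Read literally, with main effects only, there is no separate posttest or 6-month standard error to be wrong. But such a model could not test the Study Aims hypothesis of an effect at posttest that is sustained later. That hypothesis calls for occasion-specific contrasts, though the article does not write them out. If they were raw between-arm differences, the problem would almost disappear, so the choice of contrast has to be stated.

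3. **The article condenses a fuller plan.** An analysis plan that is not shown may define the residual structure or use robust standard errors, and the article does not exclude either. This lowers confidence. It does not remove the point, because the article itself names a within-person structure and does not merely leave it open.

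4. **Bias from dropout.** A reader might go further and infer that, with the 30% loss allowed for in the Power Analysis section, a wrong covariance also biases the effect estimates. Nothing here quantifies that, and the claim is not made. The figures above concern standard errors and type I error only.

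**Conclusion.** The point holds in conditional form. As stated, the primary model imposes equal variance and equal correlation on unevenly spaced occasions. If correlation falls with lag and the tests are change-from-baseline contrasts, the 6-month type I error would be about 6.4% to 10.3% in place of 5%, and the posttest standard error about 8% to 47% too large, over the range of decays assumed. The 3-month contrast is affected little. The direction follows from algebra under those two conditions; the size depends on correlations that must be assumed. It is a modest weakness in a stated choice, worth correcting before unblinded data are seen, and not evidence that the trial's result would be wrong.

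**What to change.** For each outcome, specify a linear mixed model with categorical time, condition and their interaction, and an unstructured 4x4 within-participant covariance, fitted by REML with Kenward-Roger or Satterthwaite degrees of freedom. Name the contrast to be tested at each occasion and say whether the arms share a baseline mean. Prespecify the fallback if the model does not converge: heterogeneous Toeplitz or AR(1), then a random intercept with cluster-robust standard errors. Use the same structure when results are pooled over imputed data sets.

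The cost is analysis-plan wording and ten covariance parameters in place of two, which 600 participants support easily. Compound symmetry is a special case of the unstructured form, so little is lost if correlations turn out flat. If they decay, the reported 6-month standard error will be larger than under the stated model (0.092 against 0.081 in the central case), because that is the true uncertainty.

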##### Predictors of Intervention Effects

Beyond efficacy, we will explore use-related predictors of intervention effects. Research on the dose-response relationship in internet interventions suggests that multiple adherence and engagement metrics may be relevant. For example, one study found that only the number of activities completed per log-in significantly predicted outcomes [40]. However, such relationships may depend on intervention content, delivery modality, and target population. To expand the analysis of intervention efficacy, we will examine which use-related metrics predict the intervention effects using a multiple regression model. The response variable will be the mean residualized change score from the pretest (T1) to posttest (T2) time points in the experimental condition. The predictor variables will include adherence and engagement measures.

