##### Other Metrics

Other metrics will assess treatment credibility, usage, engagement, and adherence. Treatment credibility will be operationalized as emergent credibility and measured after initial intervention exposure during the first module. We will assess credibility using the Credibility/Expectancy Questionnaire, which has shown high reliability (Cronbach α=0.85) [39]. The questionnaire items will be contextualized to reflect participation in an internet intervention. Use and engagement metrics will include completed components, completed activities, log-ins, activities per log-in, total time spent, and total words written [40]. Adherence will be defined and measured as the percentage of completed intervention activities. Additionally, we will measure subjective adherence using the following question at the posttest time point: “How accurately, in your opinion, have you completed all tasks? For example, did you follow the instructions, reflect on the questions, and respond to them exhaustively?” [22,41].

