Because meta self-efficacy is context free, it can be applied across populations and contexts, which is its substantial advantage. However, in this project, we begin by tailoring the meta self-efficacy intervention for young employees’ well-being to assess its effects in a measurable context. If this initial efficacy is established, future research should verify its applicability to other populations and circumstances. The co-creation approach can be used to adapt the context of the intervention to new populations. In the RCT phase, we will evaluate the meta self-efficacy intervention against a placebo to isolate its core effect. Consequently, our trial will not compare meta self-efficacy enhancement to a traditional context-specific self-efficacy intervention. Even if the effect size is smaller than those reported for context-specific self-efficacy interventions, meta self-efficacy may offer distinct advantages—particularly its potential for more enduring and generalizable benefits as it is hypothesized to function like a tangible skill. If we confirm this fundamental effect of meta self-efficacy, a comparison with a conventional context-specific self-efficacy intervention will become necessary. In the RCT phase, we will additionally examine how adherence and engagement, measured through multiple approaches, relate to intervention effects. While correlational, this analysis may shed light on key elements of the meta self-efficacy intervention that drive its effects and offer insight into assessing adherence in internet interventions, a question posed by previous research on the topic [41].

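### The engagement analysis regresses a residualized change score on usage metrics without naming T1 as a predictor; unless T1 is in the model, the coefficients are generally biased when usage correlates with baseline

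*Protocol article*

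**What the plan says.** The protocol article makes this analysis part of a declared aim. In Study Aims, "a secondary objective of the RCT phase is to examine how factors such as intervention engagement and adherence relate to the intervention’s efficacy".

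Predictors of Intervention Effects then sets the method:

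- The question and model: "we will examine which use-related metrics predict the intervention effects using a multiple regression model".
- The response: "The response variable will be the mean residualized change score from the pretest (T1) to posttest (T2) time points in the experimental condition".
- The predictors: "The predictor variables will include adherence and engagement measures".

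Other Metrics lists what can enter: "Use and engagement metrics will include completed components, completed activities, log-ins, activities per log-in, total time spent, and total words written". It adds adherence, as the percentage of activities completed, and a subjective adherence question at posttest.

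The status of the analysis is also stated. It is introduced with "Beyond efficacy, we will explore use-related predictors of intervention effects", and the Discussion says "While correlational, this analysis may shed light on key elements of the meta self-efficacy intervention that drive its effects".

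The article does not say on which sample T2 is regressed on T1, which outcome is meant, or how strongly usage is expected to correlate with baseline.

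**The concern.** A residualized change score is T2 with its linear dependence on T1 removed. If usage and T1 are correlated, that first step also removes the part of T2 that usage and T1 share. The second step then relates this residual to usage metrics that still carry their own T1 component. The two sides of the regression have been treated differently, so the coefficients are not in general those of a regression of T2 on T1 and usage together.

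The purpose here is to find out which metrics predict benefit, so the relative size of the coefficients is the result. The listed metrics overlap by construction (components, activities, log-ins, time, words), and overlap is what allows the bias to move from one metric to another. A correlation between baseline work self-efficacy and completing self-efficacy tasks is plausible, but the article gives no value for it.

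**Working it through.** The article states no figure for this analysis, so there is nothing to reproduce. The check is algebra plus illustration.

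**Inputs from the article.** Response and predictors as above. Total sample: "the analysis indicates that 600 participants are needed". With 1:1 allocation that is 300 per arm; less the planned 30% dropout, 300 × 0.70 = 210 in the experimental arm at posttest.

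**Inputs assumed.** The correlation r of usage with T1, the correlation between metrics, and the true effects. All are standardized and none is given in the article. Residuals are taken as fitted within the experimental arm.

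**Algebra.** Let T2 = τ·T1 + Xβ + error, where β holds the baseline-adjusted usage coefficients. Let δ be the slopes of each metric on T1, and γ the coefficients of T1 regressed on all metrics together.

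1. Regressing T2 on T1 alone gives slope τ + δ′β.
2. The residual is therefore Xβ − (δ′β)·T1 + error.
3. Regressing that residual on X without T1 gives β − γ(δ′β). The bias of metric j is −γ_j(δ′β).
4. With one standardized metric, γ = δ = r, so the coefficient is β(1 − r²).

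**One metric.** Ratio of the two-step coefficient to that from T2 on T1 plus usage, simulated with 2,000,000 observations:

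| r | ratio | 1 − r² |
|---|---|---|
| 0 | 1.000 | 1.00 |
| 0.1 | 0.990 | 0.99 |
| 0.2 | 0.960 | 0.96 |
| 0.3 | 0.910 | 0.91 |
| 0.5 | 0.750 | 0.75 |
| 0.7 | 0.510 | 0.51 |

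Adding T1 to the second step restores the adjusted coefficient: at r = 0.5 it is 0.2005 in both, against 0.1504 without T1.

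**Several metrics (population values).**

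- *Inert metric gains an effect.* Metrics correlated 0.6, r = (0.5, 0), β = (0.15, 0). γ = (0.5, −0.3)/0.64 = (0.781, −0.469); δ′β = 0.5 × 0.15 = 0.075. Coefficients: 0.15 − 0.059 = 0.091 and 0 + 0.035 = 0.035.
- *Equal effects made unequal.* Metrics correlated 0.7, r = (0.4, 0.1), β = (0.2, 0.2). γ = (0.33, −0.18)/0.51 = (0.647, −0.353); δ′β = 0.1. Coefficients: 0.135 and 0.235.
- *Modest r, strong overlap.* Metrics correlated 0.9, r = (0.3, 0.1), β = (0.15, 0). γ = (0.21, −0.17)/0.19 = (1.105, −0.895); δ′β = 0.045. Coefficients: 0.100 and 0.040.
- *Six metrics.* All correlated 0.6, r = (0.3, 0.2, 0.1, 0.3, 0.2, 0.1), β = (0.2, 0, 0, 0.1, 0, 0). Coefficients: 0.173, −0.0045, 0.018, 0.073, −0.0045, 0.018.

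**Cases without bias.**

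- Metrics correlated 0.5, r = (0.3, 0.15), β = (0.2, 0.2): γ = (0.3, 0), giving 0.173 and 0.200. The second metric is correlated with T1 yet unbiased.
- Metrics correlated 0.5, r = (0.3, 0.3), β = (0.2, −0.2): δ′β = 0, giving 0.2 and −0.2.
- All β zero: no bias in any coefficient.

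**At n = 210, one metric, nominal 5%** (3,000 replicates, T1 slope 0.6, residual SD 0.8; power at β = 0.2):

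| r | type I, two-step | type I, with T1 | power, two-step | power, with T1 |
|---|---|---|---|---|
| 0.1 | 4.8% | 4.9% | 93.7% | 93.8% |
| 0.3 | 4.0% | 4.8% | 90.7% | 92.4% |
| 0.5 | 2.4% | 5.1% | 79.2% | 87.1% |

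**The case against.** - **T1 may be in the model.** The predictor sentence is not a closed list, and this is a condensed article. That stands: the absence of T1 is an inference from what is named. However, a residualized response normally takes the place of a T1 covariate, and if T1 is intended the residualizing is redundant.
- **The residual may be fitted otherwise.** The exact factor assumes fitting within the experimental arm. If both arms are pooled, and the control slope equals the T1 slope net of usage, the one-metric factor is about 1 − r²/2, half the loss. The bias shrinks but remains.
- **The size is assumed.** At r of 0.1 to 0.3 the one-metric loss is small. With β = 0.15, residual SD 0.75 and n = 210, the standard error is about 0.75/√210 = 0.05, while the bias at r = 0.3 is 0.15 × 0.09 = 0.014. In the first two-metric example, the spurious 0.035 is about half a standard error of 0.065. This also stands, although one-metric figures do not bound the planned multiple regression, where overlap can enlarge the bias.
- **Little depends on it.** The analysis is labelled exploratory and correlational, within one arm. That limits the importance of the point but does not justify the weaker model.

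A reader might infer that every usage coefficient is wrong whenever usage correlates with baseline, or that the metrics most related to baseline are always understated. Neither follows. The bias depends on partial associations with T1 and on the unknown true effects, and the cases above include T1-correlated metrics with no bias.

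**Conclusion.** The point holds in a limited form. As described, the response is adjusted for T1 and the named predictors are not. Unless T1 is also in the regression, the usage coefficients are generally biased relative to the baseline-adjusted association when usage correlates with T1.

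For one metric the loss is r², given residuals fitted within the arm: slight at 0.3 or below and material at about 0.5. For several overlapping metrics the direction is not fixed, and the comparison between metrics, which is the aim, can be distorted.

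The size in this trial is unknown because the article gives no correlations. The efficacy analysis in Intervention Efficacy is a separate model and is not touched. The better model removes this one bias only; it does not turn a non-randomized association into a dose effect. The change is worth making because it is nearly free and serves a named secondary objective.

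**What to change.** In Predictors of Intervention Effects, replace the residualized response with: in the experimental condition, the T2 score will be regressed on the T1 score of the same outcome together with the adherence and engagement measures. At the least, keep the residualized score and state that T1 is a predictor; for a residual that is linear in T1 this gives the same usage coefficients.

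The sentence should also say what *mean* refers to. Residuals fitted within the arm average zero there, so a mean over participants cannot be the response. If a composite over outcomes is intended, include the T1 score of each component outcome as a predictor, and state how the scales (1–7, 0–4, 0–5, 1–5) are put on one metric and how job stress, where higher is worse, is oriented.

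The cost is one sentence and one degree of freedom (one per component outcome for a composite), with the same data and software.
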